#### Anthropological analysis

Data on human behaviour are analysed using a mixed methods approach, with a quantitative component nested within a broader qualitative component. The quantitative data measure the actual time individuals spend unprotected by ITNs, including classifications of types of activities and locations. This information will aid in the modeling and cross-analysis with entomological and epidemiological data. The qualitative component investigates the human behaviours that influence patterns of exposure, providing a crucial framework of analysis for the quantitative data, and are coded and analysed using ATLAS.ti or NVivo software to identify key themes.

#### Durability monitoring data analysis

The analysis of the durability monitoring component follows a prospective cohort study design of cohort nets distributed through a mass campaign, in-line with WHO and PMI standards [36, 37] for estimating the mean useful life of an ITN in operational settings. Nets are assessed at baseline and again at 12 and 24 months. The measurement for month 36 will not occur in Mozambique or Nigeria due to the time frame limitations of the grant.

Attrition, survivorship, and insecticidal bioefficacy and decay are determined at all time periods and are analysed for differences by each ITN type. Protocols for measuring the insecticidal effectiveness and insecticide content of non-pyrethroid ITNs are being developed and agreed upon throughout the partnership and will be published separately. The ITN samples are stored if reanalysis is needed once protocols have been standardized.

#### Costing and cost-effectiveness data analysis

The time horizon for cost analysis fits the duration of study, respective to setting. Costs are presented as a table of inputs, unit prices, quantities, and line item and activity codes, as possible. Costs are divided into capital and recurrent costs, based on the lifetime of the goods or service being purchased. Capital costs are discounted in the economic analysis using lifetimes determined through stakeholder interviews, expert information, and prior published literature and a discount rate of 3% (in base case scenario analysis). Varying discount rates and lifetimes are examined in sensitivity analyses. Both financial and economic analyses will be conducted. These two types of analysis show (1) financial costs (what the explicit expenses of running a programme are) and (2) economic costs (the value of all resources used during study duration). In the financial analysis, capital costs are not discounted and are applied in full at the time of purchase. All costs must be converted to a common year and currency, to ensure comparability between settings with different inflation rates and currency values. Costs are converted from local currency to US dollars using the exchange rate for the year the cost analyses are conducted. The Consumer Price Index adjustment is used to inflate or deflate all costs. Next, costs are split into two categories: tradable costs (e.g., nets) and non-tradable costs (e.g., personnel, training, supervision, social and behaviour change communication). Non-tradable costs are further converted to 2020 international dollars. This is accomplished using the purchasing power parity ratios for the countries in which the costs were incurred. For comparability and interpretability across settings, results for all countries will be presented in both 2020 US dollars and international dollars.

Costs are reported in three ways: total economic cost of the programme, total cost by activity and line item, and the total cost per output. Total cost is simply total economic cost of the mass distribution of long-lasting insecticide-treated nets over their expected lifetime. The total cost is then broken down by activity and line item. Finally, the total cost is reported as a ratio over selected outputs, such as nets distributed, sleeping spaces covered, person-years of protection, and treated net years.

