## Methods

### Study sites

The study is composed of five distinct evaluations across four countries, one each in Burkina Faso, Nigeria, and Rwanda and two in Mozambique (Table 1). In each evaluation setting, these observational pilot studies accompany the national malaria control programme (NMCP)-led mass distribution campaigns of 2019 and 2020.

**Table 1 Tab1:** Study districts, type of insecticide-treated bed nets distributed through the mass campaign, and the pre-study baseline prevalence

Country	Study area	ITN AI	ITN brand	Under 5 baseline prevalence* (%)	Primary vector species	Pyrethroid resistance status (WHO tube test mortality)
Burkina Faso [17]	Banfora	Chlorfenapyr + alpha-cypermethrin	Interceptor G2	RDT: 13.8	*An. gambiae*	High (< 50%)
	Gaoua^†^	Standard pyrethroid-only	DuraNet LN, Interceptor, MAGNet, PermaNet 2.0	RDT: 32.4	*An. gambiae*	High (< 50%)
	Orodara	PBO	PermaNet 3.0	RDT: 13.6	*An. gambiae*	High (< 50%)
Northern Mozambique [18]	Mandimba	Pyriproxyfen + alpha-cypermethrin	Royal Guard	RDT: 48.6	*An. funestus*	Moderate (85–100%)
	Cuamba	Chlorfenapyr + alpha-cypermethrin	Interceptor G2	RDT: 48.6	*An. funestus*	Moderate (85–100%)
	Gurue^†^	Standard pyrethroid-only	DuraNet LN	RDT: 44.3	*An. funestus*	Moderate (85–100%)
Western Mozambique [18]	Changara	PBO	Olyset Plus	RDT: 29.4	*An. gambiae*	High (60–85%)
	Guro	Chlorfenapyr + alpha-cypermethrin	Interceptor G2	RDT: 47.6	*An. gambiae*	High (60–85%)
	Chemba^†^	Standard pyrethroid-only	DuraNet LN	RDT: 29.4	*An. gambiae*	High (60–85%)
Nigeria [19]	Asa	Chlorfenapyr + alpha-cypermethrin	Interceptor G2	RDT: 43.7	*An. gambiae*	Variable (12–94%)
	Moro	Pyriproxyfen + alpha-cypermethrin	Royal Guard	RDT: 43.7	*An. gambiae*	Variable (12–94%)
	Ejigbo^†^	Standard pyrethroid-only	DuraNet LN	RDT: 54.9	*An. gambiae*	Variable (12–94%)
	Ife North	Alpha-cypermethrin + PBO	Veeralin	RDT: 54.9%	*An. gambiae*	Variable (12–94%)
Rwanda [20]	Karongi	Chlorfenapyr + alpha-cypermethrin	Interceptor G2	RDT: 3.1 Microscopy: 1.8	*An. funestus*	Low (85–100%)
	Nyamagabe^†^	Deltamethrin	Yahe LN	RDT: 14.4 Microscopy: 8.7	*An. funestus*	Low (85–100%)
	Ruhango	Deltamethrin (and IRS)	Yahe LN	RDT: 14.4 Microscopy: 8.7	*An. funestus*	Low (85–100%)

*IG2* Interceptor G2, *IRS* indoor residual spraying, *ITN* insecticide-treated bed net, *PBO* piperonyl butoxide, *RDT* rapid diagnostic test, *RG* Royal Guard

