### Identification of intervention and control study districts

Decisions on what brand/type of ITN to procure, and where to distribute them were made by each respective NMCP through consultation with partner institutions and international donors. The NMCPs used the dual-AI ITNs in their mass campaigns with the stipulation that there be an accompanying pilot evaluation based on their distribution and the study designs took advantage of natural comparisons among districts that results from these decisions. The NMCPs of Burkina Faso (2019) and Rwanda (2020) incorporated IG2 ITNs into their mass distribution campaigns. Mozambique and Nigeria both incorporated IG2 and RG ITNs into their 2020 mass campaigns. In addition, Burkina Faso (2019), Mozambique (2020), and Nigeria (2020) incorporated PBO ITNs into their mass campaigns. All districts included in the mass distribution campaigns receive a single type of net. A subset of districts that receive IG2, RG, PBO, and pyrethroid-only ITNs were selected by the partners as study districts (Table 2).

**Table 2 Tab2:** ITN distribution by country National Malaria Control Programmes

Geography	Study period	ITNs evaluated	ITN distribution completed
Burkina Faso	2019–2022	IG2, PBO	June 2019 (PBO) August 2019 (standard) October 2019 (IG2)
Northern Mozambique	2020–2022	IG2, RG	November 2020
Western Mozambique	2020–2022	IG2, PBO	December 2020
Rwanda	2020–2022	IG2	February 2020 (standard) May 2020 (IG2)
Nigeria	2020–2022	IG2, RG, PBO	November 2020

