The costs of each net distribution will be measured from a provider perspective and financial and economic costs calculated using an ingredients-based approach. Financial costs reflect the explicit expenditure of money associated with a programme, and economic costs reflect total resource use, or opportunity costs of a project, some of which may not be explicitly accounted for in a record of programme expenditures (such as volunteered time). The ingredients approach, or micro-costing, entails identifying all inputs to a process and assigning unit cost to each input. Costs are collected retrospectively for all campaign activities, including pre-distribution planning; household registration and community sensitization; net transportation and storage; distribution of nets to recipients; social and behaviour change communication; and monitoring and evaluation from financial and operational records, reports, pay scales, budgets, and invoices, as well as operational protocols and reports. Stakeholder interviews or resource-use survey instruments may be utilized to capture costs or resource inputs not reflected in financial or other records, such as volunteer time or assets used during the distribution but owned prior to the distribution (i.e., company vehicles), and national, regional, and local-level supervision time, or shared resources that are not included in standard financial reports. Additionally, primary cost data collection will be supplemented by a systematic review of published literature to ascertain uncertainty around measured cost estimates especially for use in probabilistic sensitivity analyses.

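### Local-currency campaign costs are converted at the analysis-year exchange rate but reported in 2020 US dollars, so currency movements after the campaigns can enter the cost figures

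*Protocol article*

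**What the plan says.** The protocol article, under *Costing and cost-effectiveness data analysis*, gives the purpose of the conversion: "All costs must be converted to a common year and currency, to ensure comparability between settings with different inflation rates and currency values". The exchange-rate rule follows: "Costs are converted from local currency to US dollars using the exchange rate for the year the cost analyses are conducted". The next sentence deals with price level: "The Consumer Price Index adjustment is used to inflate or deflate all costs". It names neither the country of the index nor a base year. Costs are then split into tradable and non-tradable items, and for the latter: "Non-tradable costs are further converted to 2020 international dollars". The paragraph closes by saying that "results for all countries will be presented in both 2020 US dollars and international dollars".

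On when the costs arise, *Study sites* says that "these observational pilot studies accompany the national malaria control programme (NMCP)-led mass distribution campaigns of 2019 and 2020". Table 2 puts completion of distribution in Burkina Faso between June and October 2019, in Rwanda in February and May 2020, and in Nigeria and Mozambique in November and December 2020. The section on cost-effectiveness of the nets adds: "Costs are collected retrospectively for all campaign activities".

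**The concern.** The rule ties the exchange rate to the year in which the analyst works, while the reporting label ties the result to 2020. A dollar figure labelled with a price year should depend on prices and rates up to that year. Under the rule as written, a supervisor's salary paid in local currency in 2020 would have a different 2020 US dollar value according to whether the analysis were run in 2021, 2022 or 2023.

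The non-tradable items that the article lists (personnel, training, supervision, communication) are those most likely to be paid in local currency. The study covers four countries, and nothing makes their currencies move together against the dollar. Total programme cost, cost by activity, and cost per net, sleeping space or person-year of protection could therefore differ between settings partly because of events after the nets were delivered.

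**Working it through.** The article states no cost, exchange rate or price index, so there is no figure to reproduce. The check is algebraic, with assumed values where numbers are needed.

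**1. Do the years differ?** The cost years are 2019 and 2020 (*Study sites*; Table 2). The price year is 2020. The analysis year is not named. Costs are collected after the event, the time horizon of the cost analysis is the study duration, Table 2 study periods end in 2022, and cost-effectiveness uses case incidence during follow-up. A final analysis in 2020 is very unlikely.

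**2. Effect on a cost incurred in 2020.** Let L be the cost in local currency, e(t) the local units per US dollar in year t, A the analysis year, and d the proportional rise in e from 2020 to A.

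- 2020 US dollar value: L / e(2020)
- Value under the rule, before any price adjustment: L / e(A)
- Ratio: e(2020) / e(A) = 1 / (1 + d)

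| Assumed d | 1 / (1 + d) | Error in local costs |
|---|---|---|
| 5% | 0.952 | −4.8% |
| 10% | 0.909 | −9.1% |
| 20% | 0.833 | −16.7% |
| 30% | 0.769 | −23.1% |
| −10% (local currency gains) | 1.111 | +11.1% |

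**3. Does the CPI sentence remove it?** A US index contains no information on d, so it cannot cancel it. If the converted amounts were treated as analysis-year dollars and deflated to 2020 with US CPI (assumed US inflation 8%), d = 20% gives 1 / (1.20 × 1.08) = 0.77, which is further from 1.

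The most favourable reading is local CPI up to year A, conversion at year A, then US CPI back to 2020. The ratio becomes (1 + local inflation) / [(1 + d)(1 + US inflation)]. With d = 20%, US inflation 8% and local inflation 10% (all assumed), this is 1.10 / (1.20 × 1.08) = 0.85. It reaches 1.00 when local inflation is 1.20 × 1.08 − 1 = 29.6%. That is the special case in which the exchange rate follows relative inflation exactly.

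**4. Total cost.** If a share s of programme cost is in local currency and the rest is invoiced in US dollars, the ratio for the total is (1 − s) + s / (1 + d). With s = 40% (assumed), d = 5, 10, 20 and 30% gives 0.98, 0.96, 0.93 and 0.91.

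**5. Incremental cost within a country.** If nets are invoiced in US dollars (assumed), the increment is (net price difference) + (delivery cost difference) / (1 + d). Where delivery costs are the same for both net types the second term is zero and d drops out.

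**The case against.** The strongest reply is that the article never says when the costing is done. It requires a common year, names 2020, and may be using the analysis year loosely for that base year; costing a campaign is also a separate step that could precede the final cost-effectiveness analysis. Index series and the order of steps normally sit in a costing protocol, and the article mentions a shared analysis framework that is not shown. This stands as far as it goes: the missing CPI details are not a fault of a condensed article, and the mismatch is very probable rather than certain. The exchange-rate sentence, however, is a stated rule, and it conflicts with the 2020 label unless the years happen to coincide.

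A reader might infer more than the text supports:

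- **That local costs will be understated by 5 to 23%.** Those figures rest on assumed currency movements and ignore any CPI step. The documents fix neither size nor sign, and a gain in the local currency reverses the error.
- **That the error vanishes only for an analysis in 2020 or an unchanged rate.** It also cancels when local CPI is used and the rate follows relative inflation. Conversely, for the 2019 Burkina Faso costs a 2020 rate is right only alongside local CPI.
- **That the article prescribes conversion first and CPI second.** The sentences appear in that order, but the only sequencing word introduces the later split into tradable and non-tradable costs.
- **That the international-dollar figures are wrong.** They inherit the problem if they are built from the converted US dollar amounts, which the wording suggests but does not state.
- **That dollar-invoiced nets are wrongly converted.** The sentence covers only costs held in local currency.

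**Conclusion.** The point holds in limited form. Fixing the exchange rate to the analysis year while reporting 2020 US dollars lets post-campaign currency movements into locally incurred costs, unless the analysis year is the cost or price year, or local CPI is used and exchange rates follow relative inflation. The only inference about timing is that the analysis falls after 2020, which follows from retrospective collection and follow-up to 2022.

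The size cannot be determined from the documents; the tabulated values show sensitivity only. The main exposure is total programme cost and cost per output, especially when compared across countries. Within-country incremental ratios are affected less where delivery costs are alike and the price difference between nets is in dollars. Prevalence and incidence effects are untouched. The rule should be corrected, but it does not threaten the epidemiological conclusions.

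**What to change.** Replace the exchange-rate sentence with one of two routes, used in every country:

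- convert each local-currency cost at the average exchange rate of the year it was incurred, then adjust to 2020 with US CPI; or
- adjust each local-currency cost to 2020 with local CPI, then convert at the 2020 average rate.

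The routes agree for costs incurred in 2020. They can differ for 2019 costs, so one should be chosen and named. For non-tradable items, derive 2020 international dollars from the 2020 local-currency values with the 2020 PPP factor, not from amounts already converted at a market rate.

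The cost is a sentence or two and a small table of rates and indices by country and year. No new data collection is needed beyond recording the year and currency of each cost line, which the financial records and invoices already being used should show.

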## Discussion

Recent gains in global reduction of malaria burden are threatened by increases in vector resistance to insecticides used in ITNs and IRS. Dual-AI ITNs provide an opportunity to accelerate progress towards reducing malaria morbidity, especially in high-risk populations with pyrethroid-resistant vectors. Dual-AI ITNs have been shown to have a higher killing impact on pyrethroid-resistant mosquitoes in experimental huts, which, if validated in the field, could further decrease transmission [13, 54, 55]. However, there remains limited programmatic evidence on the epidemiological efficacy and effectiveness—and durability of the dual-AI IG2 and RG ITNs. There are ongoing cluster randomized controlled trials occurring in coordination with NNP [56], and these are the gold standard method to empirically quantify the efficacy of these mosquito net interventions [57]. However, effectiveness determined by operational pilots in which explanatory information is collected in a robust way serve critical and complementary purposes. First, evaluations of full-scale implementation allow for measurement in a variety of settings, reflecting the diversity in the ecology and social patterns of the pilot locations, which is broadly important to the global malaria control community. Impacts from vector control can be quite different depending on the setting [10, 58, 59]. While randomized control trials are not possible in every location, pilot studies provide expanded data to further understand how these dual-AI ITNs will likely perform during mass scale-up efforts and help identify what other factors are important in considering scale-up and potential impact elsewhere. This is increasingly important within the context of scale-up of other malaria interventions, especially as the costs of ITNs rise. Second, by design cluster randomized control trials track cases in a robust and controlled manner that is infeasible in more routine health care settings given the increased levels of staff required to conduct the trials, and therefore do not reflect the experiences of NMCPs. To make the findings applicable to broader country contexts, these pilots provide analysis of routine data and are reflective of the impacts that may be seen by NMCPs during scale-up. A focus on the utility and breadth of information collected for each component will enable NMCPs and funding agencies to determine the most useful data with which to make decisions about the optimal placement of these nets based on burden, vector bionomics, human acceptability, quality, and efficiency.

The epidemiological data from routine health facilities and annual cross-sectional surveys from the four countries with varying malaria endemicity will be key in providing supporting evidence for broader scale-up and policy. In addition, the anthropological data will enhance understanding of community perceptions of the dual AI ITNs that impact their uptake and use and therefore their effectiveness in vector control. In understanding the reasons for any differences in cost-effectiveness, it is critical to understand ITN impacts on the primary and secondary vector species. The results from the entomological surveillance will also provide key evidence on the temporal and spatial patterns of vector species distributions, entomological inoculation rates, and mosquito mortality in the short to medium terms for IG2 and RG, as compared to pyrethroid ITNs or other PBO ITNs in settings where insecticide resistance is high. Evidence from physical and insecticidal durability monitoring will provide NMCPs with key information on the performance and estimated useful life of the different ITN types under different conditions and across countries, which will in turn influence their cost-effectiveness and timing of replacement net distribution. Finally, data from each component of the study will be available to inform mathematical modeling work designed to help describe and predict the effectiveness and cost-effectiveness of different net types in various malaria transmission settings and intervention contexts across sub-Saharan Africa.

One of the strengths of the NNP pilot evaluations is that they take advantage of natural comparisons that arose as the result of normal operational decisions made by partner national malaria programmes. This allows the impact of various ITN deployment strategies (including a formal evaluation of PBO ITNs in West African contexts with high intensity pyrethroid resistance caused by multiple mechanisms) to be evaluated rapidly and in real-world implementation settings, using programmatic data and public health outcomes that are most useful for national stakeholders, both for monitoring progress toward national goals and for informing future vector control decisions. However, the eco-observational, pilot designs also have many important limitations. First, though district-level observations are matched in time and, to the greatest extent possible, in ecology and geography as well, there are challenges in generating supportive datasets needed to account for fundamental differences that may exist between study districts and for potential confounding and/or co-variable factors.

This was particularly true given that campaign ITN procurement and distribution logistics required the stratification and delivery of different ITN types at the district or provincial level, so that all districts—the unit of analysis used here—within a single province typically received the same ITN type. As such, it was necessary to limit these pilot evaluations to contiguous and/or nearby districts from neighboring provinces. This approach to selecting study districts means that baseline comparisons of malaria burden and vector ecology and bionomics varied substantially both within and across the different evaluation settings, capturing real-world diversity in transmission settings but also complicating the interpretation of the observational results. While this does limit their broad generalizability, it is reflective of the diversity in which these products will be taken to scale and will provide insights into the diversity of effectiveness likely encountered through massive scale-up.

Routine health facility data provide real time insight to malaria cases and trends, but are often limited by poor data integrity, limited capacity for quality control, and supply shortages, leading to underestimation of true malaria case incidence rates. However, this robust multi-country protocol aims to ensure that the breadth of information and multiple methods of evaluation will strengthen conclusions on the cost-effectiveness of these interventions across a variety of settings in a way that a single evaluation or single measure could not.

Another source of variability, and a limitation of the study design particularly important when considering preliminary and interim results, is the relatively brief periods that were available for baseline, pre-intervention data collection given the need to align study activities with already existing regional and national-level universal coverage campaigns. The timing of campaign activities differed across study districts and so does the resulting length of time that each intervention has been deployed to date.

Due to the complexity of national malaria programming and each net distribution campaign, the protocols are not identical; however, the key ITN indicators have been harmonized across studies. A single data analysis framework has been codeveloped by study partners and is supplemented by local nuance for each individual analysis, including possibilities such as duration of net ownership, differences in measured baseline characteristics, and data gaps. In each case, if there is deviation from the main analysis plan, these actions will be described.

It is also worth noting these NNP pilot studies are not able to estimate the general impact of any (or all) ITNs relative to no ITNs, and instead they are attempting to quantify the incremental impact of dual-AI ITN types relative to standard, pyrethroid-only ITNs that still provide protection from malaria—particularly when access and use are high.

Finally, all these operational challenges were exacerbated by the ongoing COVID-19 pandemic response, and steps to account for these changes will be contextualized for during any final analysis.

